**Methods:**

The Healthy Conversations @ Playgroup randomized controlled trial (RCT) aims to address the underlying behavioral risk factors for obesity by helping parents take effective steps to improve their child’s dietary, PA, screen time, and sleep behaviors. The intervention program comprises 10 “healthy conversations” led by a trained peer facilitator, designed to increase parents’ behavioral capability and self-efficacy to implement autonomy-supportive parenting practices. The program will be delivered biweekly during regularly scheduled playgroup sessions over 10-weeks. Effectiveness will be tested in a 2-arm cluster RCT involving 60 community playgroups in three states across Australia. After baseline assessments, participating playgroups will be randomly allocated to either intervention or wait-list control conditions. Primary outcomes (vegetable intake, discretionary foods, daily PA, screen time, sleep duration, and body mass index [BMI] z-score) will be assessed at baseline, immediately post-intervention (10-weeks; T2) and 6-months post-intervention (T3). Outcomes will be assessed for differential change at T2 and T3.

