## Methods

### Study design

To address the study aims, we will conduct a multi-site cluster randomized controlled trial involving 60 community playgroups operating in three states across Australia – Queensland (*n* = 20), South Australia (*n* = 20), and Western Australia (*n* = 20). After baseline assessments, participating playgroups will be randomly allocated to either the intervention or wait-list control conditions. Primary study outcomes will be assessed for differential change immediately post intervention (10-weeks; T2) and 6-months post intervention (T3). An overview of the study design, the schedule for enrolment and study assessments is shown in Table 1.

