### Sample size and power

For Aim 1, the intervention effect is the net difference for change in the healthy lifestyle behaviors immediately post intervention and at 6-months follow-up. The research hypothesis is that the intervention will result in net differences of 0.5 serving of vegetables (38 g per day), 1.5 servings of discretionary foods per day, 15 min or 2% of time in MVPA, 30 min screen time per day, and 40 min of sleep per 24 h period. The null hypothesis is a net difference of zero. For Aim 2, the intervention effect is the net difference for change in BMI z-score at 6-months follow-up. The research hypothesis is that the intervention will result in a difference of 0.30 BMI z-score units. The null hypothesis is a net difference of zero. For a 2-year-old at the 84th percentile or a BMI z-score of 1.0, a difference of 0.30 z-score units equates to a clinically meaningful reduction of 0.4 kg in excess weight.

Table 2 reports minimal detectable differences for samples of 20, 30, and 40 community playgroups per condition. All calculations were performed assuming a power of 0.80, a 2-tailed alpha level of 0.05, an average cluster size of six parent-child dyads, and an intra-cluster correlation (ICC) of 0.10 and 0.02 for the child health behaviors and BMI z-score, respectively. Standard deviation estimates for vegetable intake were based on dietary intake data from the NOURISH randomized controlled trial [20]. The standard deviations for time in physical activity and screen time were based on previously published studies in Australian children aged 0–5 years [21]. The standard deviation for sleep duration was based on published data on Australian children [10]. The standard deviation for change in BMI z-score was based on data from the NOURISH randomized controlled trial [20]. Based on these calculations, a sample of 30 playgroups per condition achieves ≥80% power to detect the hypothesized between-group differences for each of the primary outcomes. To offset a projected attrition rate of up to 25%, an additional two children within each playgroup will be recruited, providing an overall sample of 60 community playgroups and 480 parent-child dyads.

**Table 2 Tab2:** Minimal detectable differences for child health behaviors and BMI z-score

Study Outcome	Hypothesised Effect	Est. SD	20 Playgroups (***n*** = 120)	30 Playgroups (***n*** = 180)	40 Playgroups (***n*** = 240)
Veg Intake	½ serve, 38 g/d	58 g/d	26 g/d	21 g/d	18 g/d

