### Statistical analysis

Statistical analyses will follow standard principles for RCTs using two group comparisons including all participants on an intention-to-treat basis. Between-group differences in the primary and secondary outcomes will be tested using a general linear mixed model, which accounts for the clustering of parent-child dyads within playgroups. Within each model, condition, time, the condition by time interaction will be included as fixed effects, with playgroup nested within condition, parent-child dyads nested within playgroup and condition, and the playgroup by time interaction nested within condition included as random effects.

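### As written, with independent residuals, the mixed model gives the T2 and T3 changes one common variance; if between-visit correlation falls with time, the T3 tests exceed 5% and the T2 tests are conservative.

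*Protocol article*

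**What the plan says.** Under Statistical analysis, the protocol article fits one general linear mixed model to each primary and secondary outcome. For the fixed part, "condition, time, the condition by time interaction will be included as fixed effects". The random part is playgroup within condition, with "parent-child dyads nested within playgroup and condition, and the playgroup by time interaction nested within condition included as random effects". No residual covariance is named, and no between-visit correlation or visit-specific variance appears anywhere in the article.

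The Abstract lists six primary outcomes, BMI z-score among them, and says that they "will be assessed at baseline, immediately post-intervention (10-weeks; T2) and 6-months post-intervention (T3"). Both follow-ups are inferential targets under Study design: "Primary study outcomes will be assessed for differential change immediately post intervention (10-weeks; T2) and 6-months post intervention (T3"). For BMI z-score the target is T3 alone. Sample size and power says: "For Aim 2, the intervention effect is the net difference for change in BMI z-score at 6-months follow-up". The same section sets the error rate and the clustering assumptions: "a power of 0.80, a 2-tailed alpha level of 0.05, an average cluster size of six parent-child dyads", with "an intra-cluster correlation (ICC) of 0.10 and 0.02 for the child health behaviors and BMI z-score, respectively".

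**The concern.** A dyad random intercept, a playgroup-by-time effect with a single variance and an independent residual together impose compound symmetry. Any two visits of a child are equally correlated, and the change from baseline to T2 has the same variance as the change from baseline to T3. With one follow-up this would do no harm, because there is only one change to estimate. With two it is a real constraint.

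The follow-ups are about 2.3 months (10 weeks) and 8.3 months (10 weeks plus 6 months) after baseline, in children aged 1 to 5 years. Measurements taken further apart are usually less alike. The model would then use one averaged change variance that is too small for T3 and too large for T2. Confidence intervals would be too narrow for the six-month question and too wide for the immediate one, where power would be lost. The same model serves every outcome, so one specification decides this for all of them.

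**Working it through.** **The plan's own figures.** Minimal detectable difference = (1.960 + 0.842) × SD × √(2 × DEFF / n per arm), with DEFF = 1 + (6 − 1) × ICC and n = 180 per arm (30 playgroups of 6).

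- BMI z-score: DEFF = 1.10, and 2.802 × 0.90 × √(2.20/180) = 0.279. Table 2 gives 0.28.
- Screen time: DEFF = 1.50, and 2.802 × 75 × √(3.00/180) = 27.1 min. Table 2 gives 27.
- The other four outcomes at 30 playgroups also match (20.98 g, 0.72 servings, 1.81%, 34.7 min).
- Six dyads inflated for 25% attrition make eight, and 8 × 60 = 480.

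The sample size reproduces and is not in question. It uses no between-visit correlation, so it does not help to settle this point.

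**Formula.** Let ρ be the ICC, m = 6 the dyads per playgroup, and r the correlation between two visits, taken as the same at dyad and playgroup level. With equal variances at each visit, the variance of change in a playgroup mean is proportional to 2(1 − r)[ρ + (1 − ρ)/m]. In balanced data the model as written replaces (1 − r) by its mean over the three visit pairs. The bracket cancels, so:

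- model SE / true SE = √(mean(1 − r) / (1 − r of the contrast))
- true size = 2[1 − Φ(1.96 × that ratio)]

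**Worked example** (assumed correlations: baseline–T2 0.85, T2–T3 0.75, baseline–T3 0.70). The mean of 1 − r is (0.15 + 0.25 + 0.30)/3 = 0.2333.

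- T3: √(0.2333/0.30) = 0.882, size 8.4%.
- T2: √(0.2333/0.15) = 1.247, size 1.5%.

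**Range.** All correlations below are assumptions. Simulation used 60 playgroups of 6 dyads, complete data and 40,000 replicates. The Monte Carlo standard error at 5% is √(0.05 × 0.95/40,000) = 0.11 percentage points.

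| Baseline–T2 / T2–T3 / baseline–T3 | Formula T2, T3 | Simulated, ICC 0.10: T2, T3 | Simulated, ICC 0.02: T2, T3 |
|---|---|---|---|
| Equal 0.70 | 5.0%, 5.0% | 5.0%, 4.9% | 4.7%, 4.8% |
| Weak decay 0.62/0.60/0.58 | 4.4%, 5.6% | 4.4%, 5.5% | 4.4%, 5.5% |
| Mild 0.70/0.65/0.60 | 3.4%, 6.7% | 3.4%, 6.6% | 3.4%, 6.2% |
| Moderate 0.70/0.60/0.50 | 2.4%, 8.0% | 2.4%, 8.0% | 2.4%, 7.7% |
| 0.90/0.85/0.80 | 1.6%, 9.0% | 1.7%, 9.1% | 1.6%, 8.9% |
| Serial, 0.95 per month | 0.4%, 10.2% | 0.5%, 10.0% | 0.4%, 9.7% |
| Serial, 0.98 per month | 0.3%, 10.7% | 0.3%, 10.8% | 0.3%, 10.2% |
| Equal 0.70, T2 variance × 1.3 | 5.6%, 3.9% | 5.7%, 4.0% | 5.4%, 3.7% |
| 0.60/0.60/0.65 | 5.5%, 4.0% | 5.5%, 4.0% | 5.3%, 3.7% |

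The pattern does not need decay at playgroup level. With moderate decay within dyads and a constant playgroup-level correlation of 0.80 (ICC 0.10), T2 is 3.1% and T3 is 7.2%.

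**After a fix.** A test of playgroup-mean change on 58 degrees of freedom, with its own variance for each contrast, had a size of 4.8% to 5.2% at both visits in every scenario.

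**A fix at dyad level only is not enough.** Take ρ = 0.10, so (1 − 0.10)/6 = 0.15, with correlations 0.85/0.75/0.70 at both levels. Free the dyad covariance but keep one playgroup-by-time variance.

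- T3: model variance ∝ 0.10 × 0.2333 + 0.15 × 0.30 = 0.0683; true variance ∝ 0.25 × 0.30 = 0.0750; ratio √0.911 = 0.954, size 6.1%.
- T2: model ∝ 0.0233 + 0.15 × 0.15 = 0.0458; true ∝ 0.0375; ratio √1.222 = 1.106, size 3.0%.

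**The case against.** The strongest reply is that the article says nothing about the residual. A serial or visit-specific residual could be added to the listed random effects without contradicting any word of the text, and a full plan that is not shown may do so. This stands in part. The article does not force compound symmetry, and the point must be read as conditional on independent residuals. But the article does commit to a list of model terms. On the ordinary reading of that list the constraint follows, so this is a comment on a stated model and not a request for detail left to another document.

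Second, a reader might infer that the T3 tests will run above 5% and the T2 tests well below it. The documents do not support that, because they give no correlations or visit-specific variances. Equal correlations do no harm, weak decay does little, and the last two rows of the table reverse the direction. Decay is plausible for these outcomes but is not shown for any of them.

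Third, a reader might infer that the BMI z-score test is certainly affected. It is affected only if BMI is measured at T2. The Abstract says so, but Aim 2 concerns six months only, the Table 1 schedule is not shown, and its legend does not list BMI. With BMI at baseline and T3 alone there is one change variance and no distortion. The behavioural outcomes, which are targeted at both follow-ups, would still be affected.

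**Conclusion.** The point holds in conditional form. With independent residuals, the listed random effects give one correlation and one change variance to three unequally spaced visits, although T2 and T3 are tested separately. Under assumed mild to strong decay of correlation, the nominal two-sided 5% test has a size of about 6% to 11% at T3 and about 0.3% to 3.4% at T2. At the ICC assumed for BMI z-score (0.02), the T3 range is about 6% to 10%, provided that BMI is measured at all three visits.

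These figures rest on assumed correlations, equal variances across visits, and complete, balanced data. They say nothing about attrition: how the covariance choice affects the handling of missing visits was not calculated, and no claim is made about it. The specification should be changed because the safer model is cheap and does not depend on which pattern turns out to be true.

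**What to change.** State the covariance at both levels, before outcome data are analysed:

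- Replace the dyad random intercept by an unstructured 3 × 3 within-dyad covariance over baseline, T2 and T3.
- Let the playgroup-level covariance vary by visit as well, for example with unstructured playgroup-by-time effects.
- Fit by REML with Kenward-Roger degrees of freedom, and estimate the T2 and T3 condition contrasts separately.
- Name a fallback in case of non-convergence: playgroup-level robust standard errors with a small-sample correction, or a contrast-specific analysis of playgroup-level change.
- Confirm whether BMI is measured at T2.

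The cost is modest. Two unstructured 3 × 3 matrices have 6 + 6 = 12 covariance parameters, against four in the model as written (playgroup, dyad, playgroup by time, residual), with 60 playgroups and 360 to 480 dyads to estimate them. There is some risk of non-convergence, mainly at playgroup level where the assumed ICC is as low as 0.02, and the fallback covers it. The sample size does not change.

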### Ethics

Ethical approval has been granted from the Human Research Ethics Committee of Children’s Health Queensland (HREC/19/QCHQ/66486) and administratively reviewed by The Queensland University of Technology (2000000576), Flinders University (2586) and The University of Western Australia (RA/4/20/6386). The trial has been prospectively registered with the Australian New Zealand Clinical Trials Registry (ACTRN12621000055808). Before enrolling in the trial, full written and informed consent will be obtained from legal parents/guardians. Participant data will be managed on a secured electronic database (REDCap) and hardcopy forms stored securely at the research facility.

## Discussion

As concerns for the health of young children and the resultant long-term consequences increases, light-touch universal interventions with the potential for efficient scalability and high reach are needed. In Australia, playgroups have strong engagement and acceptance within the community, but to date have been an underutilised resource in terms of health promotion. The Healthy Conversations @ Playgroup program involves providing parents the knowledge, skills, and confidence to create and manage environments for their children in which healthy behaviors across multiple domains can develop and flourish. The intervention is delivered in an ecologically-valid setting in which parents are already engaged, and likely to be open to learning through a peer facilitator. Importantly, in supporting parents as the main mechanism for change, the intervention has the potential to impact multiple children in each family setting. Through social-cognitive learning approaches, its impact may be even more broad as involved parents take on new knowledge and strategies and share them with others in the playgroup even after the research has ceased. Developmentally, supporting parenting-for-healthy-behaviors in the years prior to school is critical as it is in this time period that parents have the highest opportunity to influence their children’s lifestyle habits in ways that will support positive longer-term health trajectories.

## Data Availability

Not applicable.

## Abbreviations

BMI: Body mass index
FPSQ: Feeding Practices and Structure Questionnaire
Hz: Hertz
ICC: Intra-cluster correlation
MVPA: Moderate-to-vigorous physical activity
MBQ: Movement Behaviour Questionnaire
PA: Physical activity
RCT: Randomized controlled trial
REDCap: Research Electronic Data Capture
